**Fig. 1 Fig1:**
[figure not shown]
Study design and measurement time points (CONSORT chart). BAI = Beck Anxiety Inventory; BDI-II = Beck Depression Inventory II; BSCL = Brief Symptom Checklist; DPCCQ = Development of Psychotherapists Common Core Questionnaire; GAF = Global Assessment of Functioning; IIP-32 = Inventory of Interpersonal Problems; KIMS = Kentucky Inventory of Mindfulness Skills; PQ-M = Practice Quality-Mindfulness; SACiP = Scale for the Multiperspective Assessment of General Change Mechanisms in Psychotherapy; SCID = Structured Clinical Interview for DSM; TPI = Therapeutic Presence Inventory; WAI-SR = Working Alliance Inventory-Short Revised; CPP = Center for Psychological Psychotherapy

### Dependent variables

For an overview of the assessment measures, see Table 1.

**Table 1 Tab1:** Application plan of measures

Measures			Measurement waves			
	Pre	Session by session	Mid-5	Mid-15	Post	Follow Up
**Clinical assessment- therapists**						
Global Assessment of Functioning (GAF)	+		+	+	+	+
Development of Psychotherapists Common Core Questionnaire (DPCCQ)	+				+	+
Scale for the Multiperspective Assessment of General Change Mechanisms in Psychotherapy-Therapist (SACiP-T)			+	+	+	
Therapist techniques			+	+	+	
Allegiance scale	+		+	+	+	+
**Clinical assessment- patients**						
Structured Clinical Interview for DSM (SCID)	+				+	+
Brief Symptom Checklist (BSCL)	+		+	+	+	+
Inventory of Interpersonal Problems (IIP)	+		+	+	+	+
Beck Depression Inventory (BDI-II)	+		+	+	+	+
Beck Anxiety Inventory (BAI)	+		+	+	+	+
Scale for the Multiperspective Assessment of General Change Mechanisms in Psychotherapy-Patient (SACiP-P)			+	+	+	
Therapist techniques and study interventions (Interview by research team)					+	
Allegiance scale	+		+	+	+	+
**Mindfulness assessment-therapists**						
Kentucky Inventory of Mindfulness Skills-Therapist (KIMS-T)	+		+	+	+	+
Therapist Presence Inventory-Therapist (TPI-T)			+	+	+	
Practice Quality-Mindfulness-Therapist (PQ-M-T)			+	+	+	
**Mindfulness assessment-patients**						
Kentucky Inventory of Mindfulness Skills-Patient (KIMS-P)	+		+	+	+	+
Therapist Presence Inventory-Patient (TPI-P)			+	+	+	
Practice Quality-Mindfulness-Patient (PQ-M-P)			+	+	+	
**Session questionnaire-therapists**						
Working Alliance Inventory-Short Revised-Therapist (WAI-SR-T)		1–25				
Therapist Presence Inventory-Therapist-Short (TPI-T-S)		1–25				
Practice Quality-Mindfulness-Therapist-Short (PQ-M-T-S)		1–25				
**Session questionnaire-patients**						
Working Alliance Inventory- Short Revised- Patient (WAI-SR-P)		1–25				
Therapist Presence Inventory-Patient-Short (TPI-P-S)		1–25				
Practice Quality-Mindfulness-Patient-Short (PQ-M-P-S)		1–25				

### Primary outcome measures

Primary outcome measure 1: To assess the quality of the therapeutic alliance, we will apply the Working Alliance Inventory- Short Revised (WAI-SR; (Hatcher and Gillaspy 2006)). The WAI-SR is a 12-item self-report instrument with patient and therapist perspectives rated on a seven-point scale. It includes three subscales: bond, goals, and tasks. The bond subscale reflects the emotional relationship between patient and therapist. The goals and tasks subscales refer to the agreement of patients and therapists concerning the treatment goals and tasks. The WAI-SR is considered the gold standard for alliance assessment, has excellent psychometric properties, and is outcome predictive, as has been demonstrated in meta-analyses (e.g. (Horvath et al. 2011)).Primary outcome measure 2: To assess general symptom severity, the Global Severity Index (GSI) of the Brief Symptom Checklist (BSCL; (Derogatis and Melisaratos 1983; Franke 2000)) will be applied. The BSCL is the short version of the Symptom-Checklist-90-Revised (SCL-90-R; (Derogatis and Lazarus 1994)) and consists of 53 items forming nine subscales as follows: somatization, obsessive-compulsive, interpersonal sensitivity, depression, anxiety, hostility, phobic anxiety, paranoid ideation, and psychoticism, which are rated on a five-step scale. It showed excellent internal consistencies, with 0.71 ≤ α ≤ 0.85; good retest reliabilities, with 0.68 ≤ *r* ≤ 0.91; high correlations to the original SCL-90-R, with 0.92 ≤ *r* ≤ 0.99; and good construct validity, with scale-outcome correlations between 0.30 ≤ *r* ≤ 0.72.

### Secondary outcome measures

To assess general depressive symptoms of the patients, we will apply the Beck Depression Inventory-II (BDI, (Hautzinger et al. 1994; Beck et al. 1996)), a screening instrument for depression derived from the criteria of the DSM-IV (American Psychiatric Association 2000) that consists of 21 items on a four-step scale. It revealed an internal consistency of *α* = 0.88, a split-half reliability of *r* = 0.72, a retest reliability of *r* = 0.75, and convergent validities of 0.71 ≤ *r* ≤ 0.89.To assess general anxiety symptoms of the patients, we will apply the Beck Anxiety Inventory (BAI; (Beck et al. 1988; Margraf and Ehlers 2007)), which consists of 21 items. It revealed an internal consistency of *α* = 0.90, a split-half reliability of *r* = 0.70, a retest reliability of *r* = 0.75, and convergent validities of 0.50 ≤ *r* ≤ 0.61.To assess interpersonal functioning, we will apply the short version of the Inventory of Interpersonal Problems (IIP), which is a 32-item instrument with a circumplex structure (Horowitz et al. 1988). It consists of eight factors that are rated on a five-step scale: domineering, intrusive, overly nurturant, exploitable, nonassertive, socially avoidant, cold, and vindictive. It has excellent psychometric properties, with 0.75 ≤ α ≤ 0.94. The criterion validity of the measure has been demonstrated via correlations to the SCL-90-R with 0.07 ≤ *r* ≤ 0.75.To assess therapists’ views on the psychological, social, and occupational functioning of the patients, we will apply the Global Assessment of Functioning (GAF). This 100-point scale is divided into sections, each with ten points. The ten-point intervals have anchor points (verbal instructions) describing symptoms and functioning, while the 1–10 interval describes the most severely ill and the 91–100 interval describes the healthiest patient. The GAF is broadly acknowledged and has been applied worldwide in hundreds of studies (Aas 2010).To assess therapist variables, we will apply items of the Development of Psychotherapists Common Core Questionnaire (DPCCQ; (Orlinsky and Ronnestad 2005)). The full DPCCQ consists of 370 questions, and its psychometric properties have been demonstrated in a sample of about 5000 therapists (Orlinsky and Ronnestad 2005). We will apply the subscales of the instrument that have been found to be predictive of therapeutic processes and outcomes in several studies: difficulties in practice, warm interpersonal style, advanced relational skills, personal satisfaction, and personal burdens (Nissen-Lie et al. 2014).To assess general change mechanisms, we will apply the Scale for the Multiperspective Assessment of General Change Mechanisms in Psychotherapy (SACiP; (Mander et al. 2013)). The SACiP is a measure with six dimensions: resource activation; problem actuation; mastery; clarification of meaning; emotional bond, with three items each; and agreement on collaboration, which comprises the aspects of tasks and goals, with six items. The measure demonstrated an excellent factor structure (with 0.51 ≤ λ ≤ 0.85), revealed good internal consistencies (with 0.71 ≤ α ≤ 0.90), and was outcome predictive.To assess patients’ and therapists’ general development of mindfulness over the course of the study, we will apply the Kentucky Inventory of Mindfulness Skills (KIMS). The KIMS (Baer et al. 2004) is based on the conception of mindfulness described in dialectical behavior therapy (Linehan 1993a; Linehan 1993b) and addresses four aspects: observing, describing, acting with awareness, and accepting without judgment, with 39 items that are rated on a five-step scale. The EFA revealed an excellent factor structure with factor loadings of 0.41 ≤ λ ≤ 0.86; excellent internal consistencies, with 0.83 ≤ α ≤ 0.91; and is outcome predictive (Baer et al. 2004). Several studies replicated the four-subscale structure of the KIMS by means of factor analyses (e.g. (Ströhle et al. 2010; Baum et al. 2010)).

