### Statistical analysis

We will compare baseline descriptive statistics between the three study arms with *χ*^2^-tests (for categorical variables) and with ANOVA / t-tests (for continuous variables).

In line with the recommendations of Baldwin, Imel, Braithwaite, and Atkins (Baldwin et al. 2014), we will apply a multilevel modeling approach to address the nested data structure (sessions at level 1 are nested within patients at level 2, which are nested within therapists at level 3): Thereby, we will treat time as a within-subject factor and treatment condition as a between-subject factor. We will analyze main effects, that is, differences in intercepts of TAU + M versus TAU + PMR versus TAU concerning process and outcome variables, and interactive effects, that is, differences in slopes of TAU + M versus TAU + PMR versus TAU concerning process and outcome variables (Raudenbush and Bryk 2002). Our statistical hypothesis implies that the intercept is significantly higher in the TAU + M than in the TAU + PMR and the TAU concerning both the process and outcome variables. Additionally, it implies that the slope increases significantly stronger in the TAU + M than in the TAU + PMR and the TAU concerning both the process and outcome variables. We will conduct analyses on the intention-to-treat sample as well as on the completer sample. Furthermore, patients’ and therapists’ pre-treatment characteristics will be investigated as outcome predictors at levels 2 and 3 to control for differential effects on outcome in the three treatment arms.

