#### Bias minimization, therapist

The allegiances of therapists to the mindfulness or PMR approaches could be a potential bias (Munder et al. 2012). We will try to minimize this bias by randomizing patients (and not therapists) to the different treatment conditions in a crossed-therapist design (Falkenstrom et al. 2013). Consequently, each therapist potentially treats patients under all treatment conditions, since it is likely that different patients treated by the same therapist will be randomized to different treatment conditions. Additionally, we will apply an allegiance scale as described above. Therefore, allegiance biases will be statistically controlled. However, our sample size does not allow a perfect control for this effect. Consequently, it has to be noted as a potential limitation of the generalizability of the study results. Additionally, prior experiences with mindfulness and PMR techniques, as well as the intensity of the current mindfulness and PMR experience and practice with patients in therapy sessions, will be tested as potential confounding variables.

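### The between-arm contrasts do not exempt KIMS-T or, less clearly, the DPCCQ, although therapists are crossed with arms; a null arm difference in these traits would be uninformative

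*Protocol article*

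**What the plan says.** In the protocol article, Secondary outcome measures includes the KIMS, for patients and therapists alike, to follow the "general development of mindfulness over the course of the study". The same section introduces the DPCCQ thus: "To assess therapist variables, we will apply items of the Development of Psychotherapists Common Core Questionnaire". Table 1 schedules KIMS-T at pre, mid-5, mid-15, post and follow-up, and the DPCCQ at pre, post and follow-up.

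Statistical analysis plans to examine "differences in intercepts of TAU + M versus TAU + PMR versus TAU concerning process and outcome variables", and the corresponding slopes. The stated hypothesis is that "the slope increases significantly stronger in the TAU + M than in the TAU + PMR and the TAU concerning both the process and outcome variables". The data structure is given as "sessions at level 1 are nested within patients at level 2, which are nested within therapists at level 3". Pre-treatment characteristics of patients and therapists are also to be used as predictors at levels 2 and 3.

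Blinding, allegiance, and randomization describes a crossed-therapist design. Bias minimization, therapist adds that patients rather than therapists are randomised and that "each therapist potentially treats patients under all treatment conditions". Under Mindfulness workshop training, every participating therapist receives the mindfulness workshops.

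**The concern.** KIMS-T and the DPCCQ describe the therapist as a person. At any one time a therapist has one level of general mindfulness or personal burden, and it is the same whichever patient's file the questionnaire goes into. If practising the exercise with a TAU + M patient raises that level, the gain also appears in the forms filed for the therapist's TAU and TAU + PMR patients. Arm is assigned to the patient and is not an exposure of the therapist.

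Read literally, the generic contrasts cover these two measures. The likely harm is a misleading null: a report of no arm difference in therapist mindfulness could be taken as evidence against the route sketched in the Background (therapist mindfulness, then empathy, then alliance), when the comparison could not have shown an effect.

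**Working it through.** The plan gives no figure on this point. Its sample size of 123 concerns the time-by-condition interaction and is not used here.

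**Inputs.** 30 therapists and 150 patients (Sample and ethics), so 150/30 = 5 patients per therapist on average. Three arms with balanced blocks. Assumed: caseloads are concurrent, all therapists have the same number m of patients, and allocation is independent of therapist.

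**How far therapists are crossed with arms (m = 5).**
- At least two arms: 1 − 3(1/3)^5 = 98.8%.
- All three arms: 1 − 3(2/3)^5 + 3(1/3)^5 = 61.7%.

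**Contrast ignoring therapist.** Let the therapist's gain be proportional to the share of their patients in TAU + M, with full effect D at a share of 1.
- Expected share for a TAU + M case: [1 + (m − 1)/3]/m. At m = 5: (1 + 4/3)/5 = 0.467.
- Expected share for any other case: [(m − 1)/3]/m. At m = 5: (4/3)/5 = 0.267.
- Difference: 1/m, so 20% of D at m = 5, 50% at m = 2, 33% at m = 3 and 12.5% at m = 8. A true 0.5 SD effect would appear as 0.2 × 0.5 = 0.10 SD.

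If instead any TAU + M patient gives the full gain, the recovered fraction is (2/3)^(m − 1): again 20% at m = 5, but 67% at m = 2 and 6% at m = 8.

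**Contrast within therapist.** All of a therapist's cases carry the same trait, so the difference between that therapist's own arms is 0 for any D.

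**Planned multilevel contrast.** A model with a therapist random intercept averages the within- and between-therapist contrasts, weighted by their information. With r the correlation between two forms from the same therapist, the recovered fraction is

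w = [1/(1 − r + mr)] / {[1/(1 − r + mr)] + (m − 1)/(1 − r)}.

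At m = 5:
- r = 0.5: (1/3)/(1/3 + 8) = 4%.
- r = 0.917: 0.214/(0.214 + 48.4) = 0.4%.
- r = 0: 20%, the contrast that ignores therapist.

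A trait shared across cases implies a high r, hence about zero.

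**Simulation.** 30 therapists × 5 patients, 50 per arm, one change score per case. Assumed: between-therapist SD of change 1 and measurement SD 0.3, so r = 1/1.09 = 0.917. There were 400 data sets per row, with the mixed model fitted to 150 of them. TAU + M was compared with the other two arms together.

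| True full effect (SD) | Ignoring therapist | Mixed model | Mixed-model rejections |
|---|---|---|---|
| 0 | 0.00 | 0.01 | 5.3% |
| 0.5 | 0.08 | 0.01 | 5.3% |
| 1 | 0.18 | 0.00 | 5.3% |
| 2 | 0.40 | 0.01 | 5.3% |

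The mixed model rejects at its null rate even for a 2 SD effect.

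**The case against.** The strongest reply is that the faulty test is inferred. Statistical analysis neither says that every outcome is compared between arms nor names KIMS-T or the DPCCQ. Its wording is generic: a stronger increase under TAU + M cannot literally be the hypothesis for symptom scores. Objectives states hypotheses only on alliance and on patients' symptoms. The DPCCQ subscales were chosen because they predict process and outcome, and the abstract does not list that instrument among the secondary outcomes. An article may also leave the model for each secondary measure to a fuller document.

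Much of this stands. A reader might infer that arm tests of these two measures are explicitly planned, or that therapist mindfulness is a mechanism the trial sets out to test; the text supports neither. What remains is that both measures sit under the secondary-outcome heading with later waves, the contrasts exempt neither, and the planned predictor role covers pre-treatment values only. The crossed design is discussed for allegiance and therapist effects, not for therapist-level outcomes.

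A reader might also infer that 150 patient rows would be treated as independent information on 30 therapists. That fails, because therapists are modelled at level 3. Nor does 20% recovery describe the planned analysis: it belongs to a contrast that ignores therapist, and the planned model recovers less.

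**Conclusion.** The point holds as a minor matter of secondary outcomes, clearly for KIMS-T and less clearly for the DPCCQ. If the generic contrasts are applied to these traits, the planned three-level model gives an arm difference of about zero regardless of the true effect, so a null result carries no information on whether the exercise changes therapists.

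This rests on concurrent caseloads and on a trait that is shared across a therapist's cases. The article gives only the mean of 5 patients and says therapists potentially, not certainly, treat in all arms. Sequential cases, or a few therapists working in one arm only (about 1% at 5 patients each), would leave some weak information. The statement is therefore near-exact for the planned model and a little strong for a contrast that ignores therapist. Both primary outcomes, KIMS-P and patient-specific therapist ratings are untouched.

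**What to change.** State in Secondary outcome measures and Statistical analysis that KIMS-T and the DPCCQ are not tested between arms. Report their change over the study once per therapist (n = 30), and keep pre-study values as level-3 predictors, as already planned.

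Optionally, regress the change on the therapist's share of TAU + M patients, labelled exploratory. Its precision is low: with 5 patients each, the SD of the share is √[(1/3)(2/3)/5] = 0.21, so with a residual SD of 1 the standard error of the full effect is about 1/(0.21 × √29) = 0.88 SD.

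Keep arm tests for patient measures and for patient-specific therapist ratings (WAI-SR-T, TPI-T, GAF, SACiP-T). Limit PQ-M-T to the two arms that perform an exercise, since Demographics and other process measures defines the PQ-M as adherence control for the brief interventions and the TAU arm has none.

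The cost is analysis wording and the loss of two secondary arm tests. Data collection and the primary analyses do not change.

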
### Demographics and other process measures

Standard measures of the demographic data of patients (education level, medication, duration of illness, partnership, former psychotherapy) and the Structured Clinical Interview for the DSM (SCID) according to the DSM-5 criteria (Falkai et al. 2014) will be applied. Additionally, we will assess the intensity of the patients and therapists mindfulness and PMR experiences prior to the study; as well as the current intensity of patients’ and therapists’ mindfulness and PMR exercises conducted outside of the therapy sessions. The intensity of the mindfulness and PMR experiences will be used as a control variable in subsequent data analyses. Furthermore, we will assess adherence to the interventions.To assess patients’ and therapists’ in-session therapeutic presence, we will apply the Therapist Presence Inventory (TPI; (Geller et al. 2010)). The instrument measures the in-session presence operationalized as being fully in the present moment with an attitude of acceptance and openness. An exploratory factor analysis (EFA) revealed an excellent one-factor structure. Furthermore, the measure revealed a good internal consistency (with α = 0.75) and predicted the outcome as well as the therapeutic alliance.As for adherence control concerning the brief interventions, we will apply the Practice Quality-Mindfulness (PQ-M; (del Re et al. 2013)). The six items of the PQ-M assess the perceived quality of mindfulness implementation that is operationalized as perseverance in (a) receptive and (b) present-moment attention. The measure showed good psychometric properties, with 0.72 ≤ α ≤ 0.87, and is outcome predictive.To test potential allegiance effects, we will apply an adapted version of the allegiance scale developed by Falkenström (Falkenstrom et al. 2013). The scale consists of 30 items that assess the personal and professional attitude of therapists and patients towards TAU-M, TAU-PMR, and TAU.To assess the application of specific therapeutic techniques, we will apply an instrument that has been implemented in the CPP during the last years that measures the intensity of the CBT techniques during the last weeks. The validity of the measure has been demonstrated (Löffler et al. in press).

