### Aspects concerning bias minimization

In our nested study design, we will investigate patient and therapist contributions concerning the effects of the interventions. In contrast to double-blind medical trials, patients and therapists are informed about the different intervention groups and will actively participate in the study plan because they perform the interventions actively by themselves. This active integration of participants into the treatment plan should not be regarded as bias but rather as an important aspect of the successful implementation of psychotherapeutic interventions and as a necessary condition to implement the study design (Flückiger 2014). We will investigate the intensity of the active involvement of participants by asking specific questions concerning mindfulness and PMR experiences during the session and mindfulness and PMR practice at home and then statistically control these aspects as manipulation checks. Additionally, we will apply an allegiance scale that addresses positive and negative attitudes towards all three treatment conditions. The allegiance scale will be completed by patients and therapists and then used to control for potential bias effects of specific attitudes.

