#### Bias minimization, patient

An experienced research psychotherapist who is not involved in the study will randomly assign patients to the three different treatment conditions to reduce the potential biases of participant characteristics. All researchers and participants of the study are blind to the randomization process. Furthermore, the specific inclusion and exclusion criteria define relatively homogenous groups. Additionally, comorbidities with other psychiatric disorders, age, sex, prior experiences with mindfulness and PMR techniques, and the intensity of the current mindfulness and PMR practice will be tested as potential confounding variables. A potential limitation is that it is not possible to blind the participants concerning the different treatment groups because they will know which treatment condition they are randomized to according to the specific intervention they receive during the therapy sessions. However, this is a typical limitation of most psychotherapy studies with a randomization process (Flückiger 2014). We addressed this issue, as described above, according to the revised CONSORT statement (Zwarenstein et al. 2008; Altman et al. 2001).

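### In-session experience and home practice arise after randomisation and should not be statistically controlled in the arm comparisons

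*Protocol article*

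**What the plan says.** The protocol article speaks to this in five places.

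- *Demographics and other process measures* lists two things to be assessed in patients and therapists: "mindfulness and PMR experiences prior to the study" and, separately, the current intensity of "mindfulness and PMR exercises conducted outside of the therapy sessions". It then says: "The intensity of the mindfulness and PMR experiences will be used as a control variable in subsequent data analyses". It does not say which of the two is meant.
- *Aspects concerning bias minimization* says participants will be asked about "mindfulness and PMR experiences during the session and mindfulness and PMR practice at home and then statistically control these aspects as manipulation checks". The same paragraph says the allegiance scale will be "used to control for potential bias effects of specific attitudes". It names no measurement wave; Table 1 schedules the scale at Pre, Mid-5, Mid-15, Post and Follow Up.
- *Bias minimization, patient* names prior experience and then adds that "the intensity of the current mindfulness and PMR practice will be tested as potential confounding variables".
- *Bias minimization, therapist* does the same for therapists: "the intensity of the current mindfulness and PMR experience and practice with patients in therapy sessions, will be tested as potential confounding variables".
- *Statistical analysis* sets out a multilevel model with time, condition and their interaction, analysed by intention to treat and in completers. The only further predictors it names are pre-treatment characteristics of patients and therapists.

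Two other statements matter. *Objectives* places randomisation before therapy starts. *Experimental session* says PMR lacks the ingredients thought to make the mindfulness exercise work, namely mindful observation and acceptance.

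**The concern.** Prior experience is a baseline covariate and raises no difficulty. Experience during sessions and practice at home arise once therapy is under way, after allocation. Such variables cannot confound a randomised comparison. Where the arm changes them, they are part of how the treatment works.

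In-session experience is the clearest case. The assigned exercise is delivered in the session, and mindful attention is what should distinguish TAU + M from the other arms. Holding it constant asks what the exercise does apart from its intended mechanism, which is not what either hypothesis asks. Adjustment can also link the arm to unmeasured causes shared by practice and outcome, such as motivation or distress.

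A manipulation check is normally reported by arm to show that the manipulation took hold. Controlling for it in the outcome model is a different operation, and the article runs the two together.

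At stake is whether the reported arm effect is the effect of adding the exercise. With one section pointing to adjustment and another naming only pre-treatment predictors, both an adjusted and an unadjusted result could be presented as the planned one.

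**Working it through.** The plan gives no figure on this point, so there is none to reproduce. The check has two parts: when each variable arises, and what adjustment does to the arm coefficient.

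**Timing and stated use**

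| Variable | Arises | Stated use | Changed by arm? |
|---|---|---|---|
| Prior mindfulness/PMR experience | before the study | control variable, possible confounder | no |
| Experience during sessions | during therapy | statistically controlled | expected by design, as the exercises are assigned by arm |
| Practice at home | during therapy | statistically controlled, possible confounder | plausible, not stated |
| Therapists' practice with patients | during the study | possible confounder | depends on how it is scored |
| Allegiance | Pre and four later waves | controlled, wave not named | Pre: no; later waves: possible |

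**Algebra**

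Let A be the arm (0/1), M the post-randomisation covariate, U an unmeasured common cause with variance 1, and Y the outcome scored so that higher is better:

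- M = a·A + g·U + error, with variance 1 within arm
- Y = c·A + b·M + h·U + error

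The total effect of the arm is c + a·b. Given A and M, the expected value of U is g·(M − a·A), so the arm coefficient adjusted for M is c − a·g·h. The shift caused by adjusting is therefore −a·(b + g·h). The mediated part, a·b, is always removed. The second part, a·g·h, takes its sign from g·h. If a = 0, nothing shifts.

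**Illustration** (all inputs assumed, SD units, b = 0.3, c = 0.15, h = g)

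| a | Total, c + a·b | Adjusted, g = 0 | Adjusted, g = 0.3 | Adjusted, g = 0.5 |
|---|---|---|---|---|
| 0 | 0.15 | 0.15 | 0.15 | 0.15 |
| 0.2 | 0.21 | 0.15 | 0.132 | 0.10 |
| 0.5 | 0.30 | 0.15 | 0.105 | 0.025 |
| 0.8 | 0.39 | 0.15 | 0.078 | −0.05 |

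For example, with a = 0.5 and g = 0.5: 0.15 − 0.5 × 0.25 = 0.025. With full mediation (c = 0, a = 0.5), a total of 0.15 becomes 0, −0.045 or −0.125. Simulation with 400,000 observations agreed with the closed form to within 0.003.

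**Direction**

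Take no mediation (b = 0), c = 0.50, a = 1 and g = 0.5.

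- h = 0.4: 0.50 − 1 × 0.5 × 0.4 = 0.30
- h = −0.4 (for example, more distressed patients practise more and improve less): 0.50 + 0.20 = 0.70

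So common-cause bias can shrink or inflate the estimate. With half the effect mediated (c = 0.25, b = 0.25, total 0.50), the same two cases give 0.05 and 0.45.

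**False positives**

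Suppose the arm changes M but has no effect on Y. With 50 against 50 patients (150 over three arms), 4,000 runs and h = g, the adjusted 5% test rejected:

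| g | a = 0.5 | a = 0.8 |
|---|---|---|
| 0 | 4.6% | 4.8% |
| 0.3 | 5.8% | 5.9% |
| 0.5 | 9.8% | 15.6% |

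The unadjusted test stayed between 4.7% and 5.5%.

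This is a two-arm, single-endpoint illustration, not the planned three-arm multilevel slope model.

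**The case against.** The strongest reply is that the section defining the analysis is sound. *Statistical analysis* specifies the model, plans intention to treat and names only pre-treatment predictors. No sentence puts a post-randomisation covariate into that model, and a condensed article may leave the final covariate list to an analysis plan. This stands in part: a reader might infer that the primary estimate will be biased or the intention-to-treat analysis lost, and the article does not establish either. It does not dispose of the point, because the commitment to control in-session experience and home practice is stated outright and exempts no analysis.

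Other stronger readings are tempting and also fail.

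- The control-variable sentence in *Demographics and other process measures* does not settle the matter alone. Its wording matches experience before the study, so it is ambiguous.
- The article does not say that later allegiance scores will be adjusted for. Scheduling later waves is not a plan to use them as covariates. The defect is that no wave is named.
- Therapists' practice with patients need not be the assigned exercise. Therapists are crossed with arms, so a single value per therapist would be shared by that therapist's patients in every arm and could not absorb the within-therapist contrast.
- Home practice is not shown to differ by arm. The article does not prescribe it by arm, and total mindfulness plus PMR practice might be similar in TAU + M and TAU + PMR. If so, adjusting for it does no harm.
- The bias need not run towards no effect, as the 0.70 case shows.

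**Conclusion.** The concern holds in limited form. The article commits to statistically controlling two variables that arise after randomisation, and it treats current practice as a possible confounder, which it cannot be for a randomised comparison. For in-session mindfulness, the hypothesised active ingredient, adjustment would remove the mediated part of the effect. That conclusion needs only that the arm changes the variable and the variable affects the outcome. Further bias from common causes is possible in either direction.

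The size cannot be computed from the document; the figures above only show the range under assumed inputs. There is no bias from any covariate that the arm leaves unchanged. The article also conflicts with itself, since *Statistical analysis* names only pre-treatment predictors. Bias in the primary result is therefore a risk created by the wording, and worth removing before analysis.

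**What to change.** 1. In *Statistical analysis*, state that all primary and secondary arm comparisons adjust only for values measured before randomisation: prior mindfulness/PMR experience and the Pre wave of the allegiance scale. Confirm that both are recorded before allocation is known.
2. In *Aspects concerning bias minimization* and the patient and therapist subsections, replace control and confounder testing for in-session experience and current practice with reporting by arm as manipulation checks. Any later allegiance scores should be handled the same way. Any modelling of these variables belongs in a secondary mediation analysis labelled as such.
3. In *Demographics and other process measures*, say that the control variable is experience before the study.

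The cost is wording in these sections. No new data and no additional patients are needed, and every planned measurement can stay.
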